### Population

The study participants are patients with pDOC who will be recruited from 8 large and experienced centers of rehabilitation medicine: (1) Affiliated Rehabilitation Hospital of Nanchang University; (2) the First Affiliated Hospital of Nanchang University; (3) Ganzhou People’s Hospital; (4) the First Affiliated Hospital of Gannan Medical College; (5) Fuzhou First People’s Hospital; (6) Xinyu People’s Hospital; (7) Jiujiang First People’s Hospital; (8) Nanchang Hongdu Hospital of Traditional Chinese Medicine. Patients will be screened by trained medical personnel based on the inclusion and exclusion criteria.

Inclusion criteria: (1) Aged 18 to 65 years old; (2) Acquired brain injury patients with clear etiology; (3) Diagnosed as VS/UWS or MCS (based on 5 consecutive days of CRS-R evaluation, performed by two individuals, and consulted with a third party in case of dispute); (4) Fall in DOC up to 28 days; (5) The skin at the site of stimulation is intact; (6) Sign informed consent.

Exclusion criteria: (1) Patients whose vital signs are unstable; (2) Patients with active intracranial hypertension; (3) Patients with pacemakers, cochlear implants, or metal implants in the brain; (4) Patients with a history of cerebral nervous system disease prior to brain injury; (5) Patients with deep sedation caused by general anesthesia (e.g., propofol) or central sedatives (e.g., benzodiazepines, opioids); (6) Patients with bradycardia, atrial fibrillation, or atrioventricular block; (7) Pregnant patients.

Withdrawal criteria: (1) Recurrent seizures are difficult to control during treatment; (2) Life-threatening diseases (such as severe intracranial infections and cerebral hernia) occur; (3) Patients who consistently exhibit signs of pain below the threshold of given stimulus intensity; (4) Proactively exit.

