### Randomization and allocation concealment

The grouping scheme adopts stratified block randomization. Specifically, patients are first stratified according to the research center and then stratified according to the degree of DOC (VS/UWS or MCS). Then, patients are randomized 1:1 in variable block sizes, with stratification balancing by research center and degree of DOC. The randomization procedure is performed by independent statistical experts who are not involved in the study’s implementation or statistics. The study secretary places the generated random numbers and the grouping outcomes separately into opaque envelopes and sends them to each participating sub-center. After patients are confirmed to be enrolled, the sub-center doctors sequentially open the numbered envelopes to complete the grouping.

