### Intervention protocol

After grouping, both groups will undergo identical routine rehabilitation therapy and nursing. The active stimulation group will receive bilateral synchronized taVNS treatment (JY-VNS-200, Jingyi Medical Technology Co., Ltd., Jiangxi, China, Figure 2A). Electrotherapy is performed through a pair of metal electrodes, which are placed on the headphone-like stimulating end. The metal electrodes correspond directly to the cymba conchae and the cavum conchae (Figure 2B). Before treatment, the stimulation sites are thoroughly cleansed with alcohol to minimize impedance and ensure optimal conductivity. Treatment parameters: sine wave, 200 μs pulse width, 20 Hz frequency, 2 mA initial current intensity, 30 s on/30 s off cycle. The stimulation intensity will be gradually adjusted downwards in steps of 0.5 mA based on the patient’s tolerance (pain perception). To accurately distinguish pain from non-pain, the Nociception Coma Scale-Revised (NCS-R) will be utilized both initially and throughout the stimulation process, with a threshold of 4 points (25, 26). If the NCS-R score indicates pain (i.e., a score of ≥4), the stimulation intensity will be promptly reduced by 0.5 mA, and the NCS-R evaluation will be repeated. Patients who continue to exhibit signs of pain below the 0.5 mA threshold will be excluded from the study. To guarantee optimal contact between the electrodes and the ear skin, as well as to minimize the risk of electric burns, the device incorporates both an alarm function and a protection mechanism. These safety features will be activated whenever the electrodes fail to maintain adequate contact with the ear skin, such as when impedance exceeds 10 K Ω or the single pulse energy surpasses 8 mJ.

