**Figure 2 fig2:**
[figure not shown]
**(A)** Bilateral synchronous taVNS device; **(B)** stimulation sites and electrodes.

The device is presented with Mode A and Mode B. One is active stimulation, and the other is sham stimulation with no current output. Both modes exhibit identical screen displays and button operations (the current intensity can be adjusted, while other parameters are fixed to the values mentioned above). This makes researchers and device operators unaware of which stimulation is the active one. The two groups will receive treatment for 30 min per session, twice a day, 6 days a week for 4 weeks. The above treatment parameters and time refer to our previous single-center study (24) and peer studies (19, 23, 25). Bilateral synchronous taVNS will be performed at the same time before the start of the routine rehabilitation therapy in the morning and afternoon every day, under the operator’s continuous monitoring.

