### Data collection

After enrollment, demographics and baseline data of patients in both groups will be collected, including gender, age, cause of injury, duration of DOC, CT results (subarachnoid hemorrhage, hydrocephalus), pupillary light reflex (none, one side, both sides), cranial surgery (with or without), tracheotomy (with or without), multiple injuries (with or without), initial CRS-R, Full Outline of Unresponsiveness (FOUR), and Glasgow Coma Scale (GCS) scores.

Patients in both groups will be evaluated via CRS-R, FOUR, and GCS scores after 2 weeks of treatment and at the end of treatment (after 4 weeks of treatment). The improvement in the CRS-R scores at the end of treatment is the primary outcome. Extended Glasgow Outcome Scale (GOS-E) scores will be followed up at 3 and 6 months after the end of treatment. During follow-up, if the patients are still in the hospital, they will be evaluated in the ward. If the patients are discharged, they will be evaluated via structured phone interviews with themselves, their family members, or caregivers. According to reports, the assessment of GOS-E via phone is a valid alternative to face-to-face interviews when face-to-face contact is not possible. The level of agreement (Cohen’s weighted κ) between the two is good (27). The evaluation process during treatment and follow-up is shown in Figure 3. The total length of hospital stay and mortality during treatment and follow-up will also be recorded.

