In taVNS studies for other diseases, the current intensity was typically determined based on the patient’s perceptual threshold [e.g., 200% of the perceptual threshold (43)] or pain threshold [strongest painless stimulus (44)]. However, these methods are not applicable for patients with DOC due to their perception and communication deficits. NCS-R is a validated and highly sensitive tool for assessing the nociceptive pain responses of patients with DOC through motor, verbal and facial aspects (26). In this protocol, we use NCS-R to assess the tolerance of patients to taVNS. Specifically, the current intensity is gradually reduced in steps of 0.5 until the patients exhibit no pain response (NCS-R score < 4).

Although reports indicating that bilateral taVNS has little impact on parasympathetic nerves and is considered safe (36, 37), we will still evaluate its effects on heart rate and blood pressure. HRV serves as a crucial metric for assessing cardiac autonomic regulation by quantifying variations in sinus rhythm (28). Therefore, we will use HRV to measure the impact of taVNS on the sympathetic/parasympathetic balance. Typically, HRV is calculated using a Holter ECG, a process that can be quite intricate. Given that this is a multicenter study, the tools and methods for collecting and analyzing Holter ECG data vary significantly across sub-centers. Additionally, large-sample multicenter trials require procedures that are straightforward and easily executable. Hence, we opt for a solution involving a chest strap coupled with the EliteHRV software. This solution provides acceptable agreement compared to ECG (30, 31). In our protocol, this alternative ensures consistency, simplicity, and operability of multi-center trials.

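### Persistent pain on the NCS-R removes a randomised patient from the study instead of only ending stimulation, so the week-4 CRS-R may be lost unequally between arms

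*Protocol article*

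**What the plan says.** Randomisation is complete when the sub-centre "doctors sequentially open the numbered envelopes to complete the grouping" (Randomization and allocation concealment). Titration comes afterwards. Under Intervention protocol, stimulation starts at 2 mA and is lowered by 0.5 mA whenever the NCS-R is 4 or more. The scale "will be utilized both initially and throughout the stimulation process". The end of that path is: "Patients who continue to exhibit signs of pain below the 0.5 mA threshold will be excluded from the study". The withdrawal criteria under Population list the same event without a figure: "Patients who consistently exhibit signs of pain below the threshold of given stimulus intensity".

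Of the two device modes, "One is active stimulation, and the other is sham stimulation with no current output" (Intervention protocol, after Figure 2). Screens and buttons are identical in both, so operators are blinded.

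Under Data collection, patients in both groups "will be evaluated via CRS-R, FOUR, and GCS scores after 2 weeks of treatment" and again at the end of treatment, with GOS-E 3 and 6 months later. "The improvement in the CRS-R scores at the end of treatment is the primary outcome". The article does not say that a patient removed for pain remains under assessment.

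**The concern.** Stopping a painful stimulus is right. The difficulty is that the rule goes further and takes the patient out of the study. Ending treatment and ending observation are separate decisions, and only the first is needed for safety.

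The trigger is also partly a result of treatment. A sham patient can score 4 or more through spontaneous behaviour or handling, but only an active patient can do so because of the current. Blinding stops operators from applying the rule differently by arm. It does not make the trigger occur equally often in the two arms.

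The NCS-R rates motor, verbal and facial responses (Discussion), so patients who meet the criterion may differ in responsiveness from those who do not, and perhaps in how much they would improve. If so, and if removals differ by arm, the week-4 comparison is no longer between the groups as randomised. Removed patients also use up the 10% loss allowance although they could still be assessed.

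**Working it through.** **1. Order of events.** Envelope opened; arm assigned; titration at 2.0, 1.5, 1.0 and 0.5 mA; NCS-R still 4 or more; patient removed. The earliest point is the first session. The week-2 and week-4 CRS-R both come later.

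**2. The plan's own figure** (Sample size section: 10.93 ± 4.99 against 9.28 ± 4.38, power 90%, α 0.05, equal arms; two-sided assumed).
- Difference = 10.93 − 9.28 = 1.65.
- Common SD = √((4.99² + 4.38²)/2) = 4.695.
- n per arm = 2 × [4.695 × (1.960 + 1.282)/1.65]² = 170.1, so 171. The t-based solution is 171.1, so 172, as stated.
- 344/0.9 = 382.2, stated as 382, or 191 per arm.

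The stated sample size reproduces, and this point does not change it.

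**3. Possible bias.** In each arm the mean improvement of those kept differs from that of all patients by f × d. Here f is the share removed and d is the mean improvement of kept minus removed patients. The comparison therefore shifts by (f active − f sham) × d. The article gives neither quantity, so both are assumed:

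| Net imbalance | d = 1 point | d = 2 points | Share of 1.65 |
|---|---|---|---|
| 2 percentage points | 0.02 | 0.04 | 1–2% |
| 5 percentage points | 0.05 | 0.10 | 3–6% |
| 10 percentage points | 0.10 | 0.20 | 6–12% |

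Sham removals reduce the imbalance: 10% active with 5% sham gives the middle row. The sign of d is unknown, so the direction is too.

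For scale, take an assumed within-patient correlation of 0.6 to 0.8. The standard error of the difference in change is 4.695 × √(2(1 − ρ)) × √(2/172), which is 0.45 to 0.32. A bias of 0.05 to 0.10 would then move a nominal two-sided 5% error to between 5.1% and 6.1%.

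**4. Loss allowance.** 191 − 172 = 19 per arm. Removing 5% of the active arm (0.05 × 191 = 9.6) would use about half of it.

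**5. Power if patients are kept** (noncentral t, SD 4.695, 172 in the sham arm). If a share x of the active arm stops and gains nothing, the effect becomes 1.65 × (1 − x). The credited column treats these patients as otherwise part of the 10% loss, so keeping them makes the active arm 172 + 191x. The last column removes them on top of that loss, leaving 172 × (1 − x) active patients at an effect of 1.65.

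| x | Diluted effect | Power, 172 per arm | Power, retained patients credited | Power if removed |
|---|---|---|---|---|
| 0 | 1.65 | 90.1% | 90.1% | 90.1% |
| 2% | 1.62 | 89.0% | 89.3% | 89.9% |
| 5% | 1.57 | 87.0% | 87.9% | 89.4% |
| 10% | 1.49 | 83.3% | 85.1% | 88.5% |

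**The case against.** **Silence in a condensed article.** Nothing says that assessments stop, and Data collection schedules them for both groups without exception. A full protocol may settle what happens after withdrawal. This has some force, and it is why the point is that the week-4 CRS-R may be lost. But a general schedule does not override an explicit instruction to exclude a patient from the study, and that instruction is stated twice.

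**Too many unknowns.** Bias needs an appreciable removal rate, an imbalance between arms, a different course in those removed, and uncollected data. The article quantifies none of these. Four active settings come before removal, and the earlier single-centre trial reported no significant side effects. That trial stimulated only the left ear, so it is weak evidence for bilateral stimulation. The objection stands as to size.

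**The remedy costs more power than the rule.** This is true if stopped patients gain nothing, as the last table shows. But the higher power under removal is for an effect among patients who tolerate the current, not for the groups as randomised.

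**The floor wording.** Because the Discussion says that "the current intensity is gradually reduced in steps of 0.5 until the patients exhibit no pain response (NCS-R score < 4" and names no floor, a reader might infer that an active patient could carry on at 0 mA. The documents do not support that. The Discussion passage summarises titration, does not contradict the Intervention protocol, and does not govern conduct. The evident intent is pain persisting at 0.5 mA, the lowest active step. The missing figure in withdrawal criterion 3 calls for clarification and is not a contradiction.

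**Conclusion.** The point holds as a minor one. The article fixes a conduct rule that can take randomised patients out of the study for a reason partly caused by the active treatment, before the primary outcome is measured. An analysis plan can choose how to handle missing values, but it cannot supply a CRS-R that was never taken.

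The likely size is small: the middle row of the bias table is a reasonable illustration, but it rests entirely on an assumed imbalance and an assumed difference in improvement.

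A reader might go further and infer that removed patients are dropped from the analysis, that removals will certainly be unequal, or that the trial's error rate is seriously inflated. The article does not say the first. The second is plausible, but sham patients can also meet the criterion. The third would need a removal rate that the article does not give.

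**What to change.** Change two places, withdrawal criterion 3 under Population and the exclusion sentence under Intervention protocol, so that both carry one rule: 0.5 mA is the lowest setting in either mode; if the NCS-R remains 4 or more there, stimulation stops permanently, the patient stays in the study, all scheduled CRS-R, FOUR, GCS and GOS-E assessments continue, and the patient is analysed in the arm assigned. The Discussion needs no edit.

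The safety purpose and the blinding are unaffected, because the same displayed setting triggers the same action in both modes. The assessments are already scheduled. The cost is dilution: on the pessimistic assumption that stopped patients gain nothing, power falls below the planned 90% as in the last table, modestly at 2% and noticeably at 10%. The sponsor should accept this knowingly. The change is worth making while patients are still being assessed, because it cannot be made in retrospect.

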**Figure 2 fig2:**
[figure not shown]
**(A)** Bilateral synchronous taVNS device; **(B)** stimulation sites and electrodes.

The device is presented with Mode A and Mode B. One is active stimulation, and the other is sham stimulation with no current output. Both modes exhibit identical screen displays and button operations (the current intensity can be adjusted, while other parameters are fixed to the values mentioned above). This makes researchers and device operators unaware of which stimulation is the active one. The two groups will receive treatment for 30 min per session, twice a day, 6 days a week for 4 weeks. The above treatment parameters and time refer to our previous single-center study (24) and peer studies (19, 23, 25). Bilateral synchronous taVNS will be performed at the same time before the start of the routine rehabilitation therapy in the morning and afternoon every day, under the operator’s continuous monitoring.

### Blinding and unblinding

The study is a double-blind design. The A/B Mode of the device effectively blinds the researchers. The participants are patients with pDOC who remain unaware of the study’s specifics. Furthermore, the evaluators and data analysts are kept blind to the grouping of patients. After the trial, the person in charge of blinding who did not participate in the study will break the blinding. When patients experience serious complications (such as cardiac arrest) during the trial and they are suspected to be related to taVNS, the sub-center can call the person in charge of blinding for emergency unblinding.

### Data collection

After enrollment, demographics and baseline data of patients in both groups will be collected, including gender, age, cause of injury, duration of DOC, CT results (subarachnoid hemorrhage, hydrocephalus), pupillary light reflex (none, one side, both sides), cranial surgery (with or without), tracheotomy (with or without), multiple injuries (with or without), initial CRS-R, Full Outline of Unresponsiveness (FOUR), and Glasgow Coma Scale (GCS) scores.

Patients in both groups will be evaluated via CRS-R, FOUR, and GCS scores after 2 weeks of treatment and at the end of treatment (after 4 weeks of treatment). The improvement in the CRS-R scores at the end of treatment is the primary outcome. Extended Glasgow Outcome Scale (GOS-E) scores will be followed up at 3 and 6 months after the end of treatment. During follow-up, if the patients are still in the hospital, they will be evaluated in the ward. If the patients are discharged, they will be evaluated via structured phone interviews with themselves, their family members, or caregivers. According to reports, the assessment of GOS-E via phone is a valid alternative to face-to-face interviews when face-to-face contact is not possible. The level of agreement (Cohen’s weighted κ) between the two is good (27). The evaluation process during treatment and follow-up is shown in Figure 3. The total length of hospital stay and mortality during treatment and follow-up will also be recorded.

**Figure 3 fig3:**
[figure not shown]
Evaluation process. CRS-R, Coma Recovery Scale-Revised; FOUR, Full Outline of Unresponsiveness; GCS, Glasgow Coma Scale; GOS-E, Extended Glasgow Outcome Scale.

The cardiovascular system is doubly innervated by the sympathetic and parasympathetic nerves. The vagus nerve is a mixed cranial nerve that contains parasympathetic nerve fibers. In theory, stimulating the vagus nerve may increase the risk of its mediated bradycardia and hypotension. Heart rate variability (HRV) analysis can provide information on the balance between the sympathetic and parasympathetic pathways (28). It is a useful tool for evaluating cardiac autonomic regulation (28). Therefore, we will use a heart rate chest strap (Maijin Intelligent Technology Co., Ltd., Qingdao, China) and the Elite HRV smartphone application (Elite HRV Inc., Asheville, NC, United States) to collect and analyze patients’ HRV information. Specifically, placing the sensor of the chest strap at the level of the heart in front of the chest. Adjusting the length of the elastic strap to ensure close contact between the electrode area and the skin. Connecting the chest strap to the Elite HRV application on the phone via Bluetooth. We will collect and analyze HRV information of the patients for 30 min before and during the first taVNS, including mean heart rate, mean RR, the standard deviation of normal-to-normal RR intervals (SDNN), the root mean square of successive differences (RMSSD), the proportion of NN50 divided by the total number of normal-to-normal RR intervals (PNN50), low-frequency (LF) power, high-frequency (HF) power, total power, and LF/HF ratio. The chest strap records the cardiac electrical activity and extracts heart rate data from the electrocardiogram (ECG) waveforms, which has detection results comparable to Holter ECG (29–31). For blood pressure, we will record it once separately before and during the patient’s first taVNS. In addition to our recordings, ECG monitoring will also be performed on patients during each stimulation to detect vital signs.

Poor skin and electrode contact may lead to skin burns. Although the device provides burn risk alarm and protection mechanisms, we will still record skin burns at the stimulation sites, including exudation, blisters, and other skin damage. We will record any adverse events that may occur in various systems during the trial period, which may affect the patient’s prognosis. These include epilepsy, paroxysmal sympathetic hyperactivity, hydrocephalus, intracranial infection (nervous system); deep vein thrombosis, pulmonary embolism, cardiac arrest (cardiovascular system); pulmonary infection, acute respiratory distress syndrome (respiratory system); gastric bleeding (digestive system); and urinary tract infection (urinary system). These adverse events are largely unrelated to taVNS. In addition, we will collect records on the type and volume of routine rehabilitation therapy for both groups during the trial period.

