**Methods:**

We aim to recruit 382 patients with prolonged DOC, and divide them into an active stimulation group and a sham stimulation group. The patients in the active stimulation group will receive bilateral synchronous taVNS with a 200 μs pulse width, 20 Hz frequency, and personal adjusted intensity. The sham stimulation group will wear the same stimulator but without current output. Both groups will receive treatment for 30 min per session, twice per day, 6 days per week lasting for 4 weeks. The clinical assessment including Coma Recovery Scale-Revised (CRS-R), Full Outline of Unresponsiveness (FOUR), Glasgow Coma Scale (GCS), and Extended Glasgow Outcome Scale (GOS-E) will be conducted to evaluate its efficacy. Heart rate variability (HRV), blood pressure, and adverse events will be recorded to evaluate its safety.

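### Pain responses to stimulation drive the titration but are in none of the named safety outcomes, so those settled by lowering the current would not be reported by arm

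*Protocol article*

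**What the plan says.** **Pain.** The Intervention protocol section applies the NCS-R at the outset and again during stimulation, with a cut-off of 4 points: "If the NCS-R score indicates pain (i.e., a score of ≥4), the stimulation intensity will be promptly reduced by 0.5 mA", after which the scale is repeated. The Discussion gives the purpose as judging tolerance. Persistent pain is a withdrawal criterion in the Population section, and the Intervention protocol removes patients who still show pain below the lowest step.

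**Safety.** The Abstract names three measures: "Heart rate variability (HRV), blood pressure, and adverse events will be recorded to evaluate its safety". The Data collection section describes HRV and blood pressure before and during the first session. It then adds a local harm, "we will still record skin burns at the stimulation sites, including exudation, blisters, and other skin damage", and a general one: "We will record any adverse events that may occur in various systems during the trial period, which may affect" prognosis. Eleven systemic complications follow as examples, with the comment "These adverse events are largely unrelated to taVNS". The Statistical analysis section plans paired tests for HRV and blood pressure, and a chi-square or Fisher's exact test of adverse event incidence between groups.

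None of these safety passages mentions pain, NCS-R scores, intensity reductions or the intensity finally used.

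**The concern.** The trial sets out to give evidence on safety as well as efficacy, in patients who cannot say that something hurts. The protocol treats pain as a foreseeable effect of the current and has staff watch for it in order to set the intensity. That information then appears in no safety outcome.

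Adverse event incidence is the only safety measure that the Statistical analysis section says will be compared between arms. Apart from burns, it is illustrated by complications that the authors expect to have little to do with the device. A report following this text could call the treatment safe without saying how many patients showed a pain response, or how far the current had to be lowered. If the sham arm is scored in the same way, it would supply the background rate of high NCS-R scores from spontaneous behaviour, and the excess in the active arm could be estimated. That comparison is what stands to be lost.

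**Working it through.** **1. Is pain in any named safety measure?**

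- HRV and blood pressure (Abstract, Data collection, Statistical analysis): physiological readings around the first session. Pain is not among them.
- Skin burns (Data collection): exudation, blisters and other skin damage. Pain without a lesion is not covered.
- Adverse events (Abstract, Data collection, Statistical analysis): described by possible effect on prognosis and illustrated by eleven systemic complications such as pulmonary embolism and pulmonary infection. A brief pain response that ends when the current is lowered does not naturally fit.
- Withdrawals (Population, Intervention protocol): cover pain that persists, not pain that titration resolves.

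The unreported part is therefore pain resolved by titration.

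**2. Planned size.** The Sample size section gives 10.93 ± 4.99 against 9.28 ± 4.38, 90% power and α = 0.05.

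- Difference = 10.93 − 9.28 = 1.65; SD = √((4.99² + 4.38²)/2) = 4.695.
- A two-sided t-test needs 171.1 per arm, rounded up to 172. Allowing for 10% loss, 2 × 172/0.9 = 382.2.

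The plan's 172 and 382 reproduce. The point does not depend on them; they only give 382/2 = 191 per arm.

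**3. Amount of observation.** Two sessions a day, six days a week, for four weeks is 2 × 6 × 4 = 48 sessions per patient, and 191 × 48 = 9,168 per arm. This is a planned maximum: it assumes that every patient completes every session, and the number of NCS-R scores per session is not stated.

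**4. Could the trial estimate the rate?** No pain rate is given, so a range is assumed for the share of active patients with at least one pain response. The 95% Wilson interval is

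(p + z²/2n ± z√(p(1−p)/n + z²/4n²)) / (1 + z²/n), with n = 191 and z = 1.96.

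| Assumed rate | Patients | 95% interval |
|---|---|---|
| 2% | about 4 | 0.8% to 5.1% |
| 5% | about 10 | 2.7% to 9.1% |
| 10% | about 19 | 6.5% to 15.1% |
| 20% | about 38 | 14.9% to 26.2% |
| 30% | about 57 | 23.9% to 36.8% |

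With 172 patients instead of 191, the 10% row becomes 6.4% to 15.4%.

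**5. Precision of a between-arm difference.** For assumed rates of 30% active and 10% sham, the half-width is 1.96 × √(0.3 × 0.7/191 + 0.1 × 0.9/191) = 0.078, so a difference of 20 points would carry about ± 8 points. This shows precision only and does not predict a result.

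**The case against.** **The adverse event sentence is ambiguous.** It opens with a broad scope, the clause on prognosis can be read as description, and the list is not closed. A site could log a pain response under it. This stands, so one cannot say that the text forbids recording pain. But every example is a major complication, and nothing in the sentence prompts a site to enter a brief pain response.

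**This is an article.** The Data management section refers to a case report form and a predetermined analysis plan, and either could hold these items. That is fair as far as data fields go. The article does, however, itself state the scope of adverse events and the safety analyses, in enough detail to name blisters and individual HRV indices. The comment is on the scope it sets.

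**Persistent pain is visible.** The Study design section commits the report to CONSORT, so withdrawals for pain would probably appear in the participant flow. This stands, and it rules out the reading that all pain would go unreported.

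**Other harms are better covered.** Bradycardia, hypotension and burns are also named as risks, and each has planned measurement. The documents do not rank pain above them.

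**Sham scoring is not stated.** It is inferred from the two modes having the same display and adjustable intensity. The between-arm comparison depends on it.

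A reader might also infer a contradiction with the Blinding and unblinding section, which provides emergency unblinding "When patients experience serious complications (such as cardiac arrest) during the trial and they are suspected to be related to taVNS", while cardiac arrest is also on the list described with "These adverse events are largely unrelated to taVNS". The texts do not support that. The second statement is qualified, the first is conditional on suspicion, and the incidence comparison has no relatedness condition, so no event is removed from the analysis.

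**Conclusion.** The point holds in a limited form. The protocol scores pain in order to set the intensity and names no safety outcome into which a response resolved by titration naturally falls. As written, such responses would not be compared or reported by arm. This weakens what the trial can say about tolerability. It does not affect the primary analysis or make any stated safety analysis invalid.

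The size of the unreported harm cannot be given. It would be wrong to infer that a clear harm signal is being left out: the rates used above are assumptions, and a low true rate would be reassuring. What can be concluded is that about 191 patients per arm would give a usable estimate across assumed rates of 2% to 30%. The conclusion rests on the natural reading of the adverse event sentence; the between-arm comparison also needs NCS-R scoring in both arms.

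**What to change.** In the Data collection and Statistical analysis sections, add as safety outcomes by arm:

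- the proportion of patients with any NCS-R score of 4 or more;
- the number of intensity reductions;
- the settled current;
- withdrawals for pain.

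State that the NCS-R is scored in the same way and at the same times in both arms. Drop the prognosis qualifier so that all adverse events are recorded. These are recording and reporting changes; the titration rule stays as written.

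As a minor wording point, replace the blanket statement on relation to taVNS with a blinded judgement of relatedness for each event.

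The cost is a few case report form fields for scores and settings that already arise at the bedside, and one extra table. The safety profile may look less favourable as a result.
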